### Data collection

The data items for each component of the study are summarised in Table 1. The interventions will run in LGAs for a nine to twelve month period depending on birth numbers available in participating LGAs. The first two months of the interventions will be a pilot phase/run-in period. This will give SILC-MCHNs the opportunity to provide feedback on issues they may encounter and the research team the opportunity to refine protocols. Data collected during the run-in period will not be used in the final analysis.

**Table 1 Tab1:** **Data collection for SILC**

Data collection time-point	SILC-MCHN visit assessment	SILC-MCHN visit	Drop-in centre visit	4 month KAS visit	8 month KAS visit	SILC postal survey	IV close
**Maternal data**							
Date of birth	X	X					
Age				X		X	
Parity		X	X	X		X	
Health care card status				X		X	
Income level						X	
Aboriginal/Torres strait islander status				X		X	
Marital status						X	
Highest education attainment						X	
Smoking status (current and in pregnancy)						X	
Alcohol consumption (current)						X	
Maternal height and weight						X	
Employment status						X	
Country of birth				X		X	
Year arrived from overseas				X		X	
Residency status						X	
Current postcode of residence			X			X	
Breastfeeding intention						X	
Infant feeding support after hospital discharge						X	
Breastfeeding complications after hospital discharge						X	
Reasons for ceasing/not commencing breastfeeding						X	
Knowledge and use of community infant feeding services						X	
**Paternal data**							
Country of birth				X			
**Birth data**							
Method of birth				X		X	
**Infant data**							
Date of birth	X	X		X		X	
Gestational age at birth				X			
Infant age			X	X	X	X	
Infant feeding ‘in the last 24 hours’	X	X		X		X	
Infant feeding at three months of age				X			
Infant feeding at six months of age					X		
Infant age at breastfeeding cessation						X	
Infant age at introduction of infant formula						X	
Infant age at introduction of solids						X	
**MCH centre data**							
MCH centre postcode				X	X		
**Process evaluation data**							
Number of women assessed, eligible for, received and declined SILC-MCHN visit	X						
Length of SILC-MCHN visits		X					
Topics discussed, factsheets provided and website information provided during SILC-MCHN visits		X					
Reason(s) for visiting SILC drop-in centre			X				
First or subsequent visit to SILC drop-in centre			X				
**SILC-MCHN data**							
Evaluation of SILC trial via focus groups and surveys							X
**MCH co-ordinator data**							
Evaluation of SILC trial via interviews							X

KAS= Key Ages and Stages visit, IV= intervention, MCH= Maternal and Child Health, SILC-MCHN= SILC Maternal and Child Health Nurse.

#### Baseline data

Baseline breastfeeding rates will be collected to allow a before and after analysis of breastfeeding rates in each LGA, and to assess comparability of trial arms at trial commencement. Baseline breastfeeding outcomes will be collected for a period of three months before infants exposed to the interventions will have their routine MCH appointments (when breastfeeding outcomes are collected). These data will be obtained from routinely collected MCH centre data (three, four and six month infant feeding data) and from a new data item to collect infant feeding ‘in the last 24 hours’ (in all participating LGAs). Inclusion of this new data item will give higher quality cross-sectional data, enhancing the capacity to discern changes that may arise from the intervention. It will be completed by MCHNs with mothers at their routine four month KAS visit.

#### Outcome data

There will be two components to outcome data collection. Breastfeeding outcomes will be obtained from routinely collected MCH centre data and from the new data item collecting infant feeding ‘in the last 24 hours’ at four months.

In addition, information will also be obtained directly from women via a postal survey. All women who give birth during the intervention time-frame in the participating LGAs will be sent a questionnaire when their infants are six months of age, with the exception of those who meet the exclusion criteria described previously. Data will include socio-demographic details and infant feeding outcomes (*any* breastfeeding at survey completion, and duration of *any* and *only* breastfeeding). Women will be asked if they have had difficulties with breastfeeding, and if and where they obtained support or help with breastfeeding. Information will also be collected about home visiting (as part of the intervention or other home visiting services) and breastfeeding services (including the intervention drop-in centres). Women will be given the opportunity to report on their views and experiences of the available services.

#### Outcome variables

The primary outcome of the study is *any* breastfeeding at four months. A single data item asking about *infant feeding* ‘in the last 24 hours’ will be used to ascertain this outcome at the routine four month KAS visit. The four month KAS participation rate from the last state-wide report was 93.6% [43]. Three and six month infant feeding outcomes will be obtained from routinely collected MCH centre infant feeding data collected at the four month and eight month KAS visits respectively. The eight month KAS participation rate from the last state-wide report was 85.6% [43].

Other variables of interest (or potential confounders for the primary outcome) which will be abstracted from routinely collected MCH data are:Gestational age of infant at birth;Date of birth of infant;Parity of mother;Mode of birth (vaginal, caesarean delivery);Age of mother;Date of the routine four month KAS visitInfant age in weeks at the routine four month KAS visit;Health Care Card [proxy for socioeconomic status];Aboriginal/Torres Strait Islander status of mother;Country of birth of mother;Year mother arrived from overseas (where relevant);Country of birth of father; andMCH centre postcode.

For the secondary aims of the study, addressed via the survey exploring women’s satisfaction with the breastfeeding support they received, the following variables will be collected:Infant feeding at six months;Introduction of solids;Infant feeding intention;Breastfeeding complications, such as milk supply issues, nipple pain and mastitis;Reasons for not commencing breastfeeding;Reasons for ceasing breastfeeding;Breastfeeding support after discharge (domiciliary visits, Lactation Consultant, MCHN, SILC-MCHN, MCH line, ABA, breastfeeding drop-in centre);Woman’s knowledge of community breastfeeding services available (SILC-MCHN, breastfeeding drop-in centre); andBackground data such as maternal age, marital status, education, income level, employment status, smoking status, and maternal height and weight.

Intervention implementation – process and impact measures:Assessment of adherence to intervention protocols;Evaluation of the SILC trial via surveys and focus groups with SILC-MCHNs; andInterviews with MCH co-ordinators.

### Data analysis

Data from SILC-MCHN and drop-in centre logs will be entered into a Microsoft Access database [44]. Data from questionnaires will be entered by a data-entry company. All data will be analysed using Stata Version 13 [45].

#### Primary outcome

In relation to the trial hypotheses, each intervention group will be compared to the standard care group using intention to treat analysis. For the primary outcome, proportions of women giving their baby *any* breast milk at four months will be compared using odds ratios derived using logistic regression. A multivariate analysis will be carried out to adjust for known potential confounders, as well as for the baseline breastfeeding rates of each LGA. In all analyses, adjustment will be made for clustering at the MCH centre level, and the LGA strata (i.e. LGA size) will be taken into account. Results will be presented as adjusted odds ratios, with 95% confidence intervals.

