### Intervention allocation

#### Randomisation procedure

Due to the nature of the intervention blinding is not possible. The unit of randomisation will be the LGA. Eligible LGAs will be randomly allocated to one of the three trial arms, stratified by the number of births (Figure 1). To ensure the process is open and transparent, allocation to trial arms will take place at a public forum to which representatives from participating LGAs will be invited. Prior to the forum the eligible LGAs will be grouped according to the number of births (large, medium, small), their name recorded on paper and placed in individual sealed opaque envelopes. An independent audience member (not linked to any of the participating SILC LGAs) will be invited to assist with the process. LGAs in the large group will be randomised first, followed by LGAs in the medium group and then the small group. The audience member will shuffle the envelopes with LGAs from the large group and select one envelope at random. This LGA will be assigned to the comparison arm. Another envelope will then be chosen by the audience member. The LGA in this envelope will be assigned to Trial arm 1 (the early home-visiting arm). The remaining envelope will then be opened. The LGA in this envelope will be assigned to Trial arm 2 (the early home-visiting plus drop-in centre arm). This process will then be repeated for the medium and for the small LGA group.

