While the unit of randomisation is the LGA, the MCH centres form the clusters. We aim to have the power to detect an increase in the overall breastfeeding rates at four months from 48% to 58%. With this change and assuming a standard error for the average breastfeeding rate in each LGA of 5%, sample size estimates show that we need approximately 4 LGAs in each trial arm. To achieve this standard error we need to have 374 women in each arm (without allowing for clustering). Given that we will be obtaining breastfeeding data on all women in each LGA, with an estimated average of about 1000 births per LGA per annum, we can obtain the required sample size allowing for an inflation factor of approximately 2.7 (1000/374), which if the *geometric* mean number of MCH centres is 86 (calculated on data from MCH centres in the potentially eligible LGAs), allows for an intra-cluster correlation (ICC, ρ) of 0.02 (2.70= 1 + 85*ρ). We could not identify relevant literature on which to base our estimate for the ICC in breastfeeding trials, therefore we used the conservative estimate of 0.02 which is larger than ICCs found in cluster trials for smoking cessation in pregnancy [42]. This was also consistent with the variation we found in state-wide MCH data.

Calculating the number of women who will be eligible to potentially receive the intervention is based on the fact that the proposed intervention will only have the ability to affect women who are breastfeeding at discharge, so to gain this 10% increase overall (i.e. 48% to 58%) we will need to increase the rate of breastfeeding from 59% (or 48%/81%*100) to 72% (58%/81%*100) among those who are breastfeeding at hospital discharge. For a simple random sample this would require 224 women per each intervention trial arm (with alpha 0.05 and 80% power), i.e. 448 in total. Taking into consideration the potential effect of clustering we have inflated the sample size assuming an intra-cluster correlation (rho) of 0.02 (as discussed above), so we require approximately 400–500 women in each intervention arm.

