### Trial status

Twenty one Victorian LGAs were eligible to participate in SILC. Eighteen of these LGAs submitted a written Expression of Interest to participate. Following briefing sessions with these 18 LGAs, four were deemed ineligible to participate as they had ongoing initiatives in place similar to one or both of the interventions. A further four declined to participate. The remaining ten LGAs, comprising three large, three medium and four small LGAs, agreed to participate and be randomised. During randomisation, one LGA from each group (small, medium, large) was randomly assigned to be the comparison LGA for that group, one was assigned to receive home-visits by a SILC-MCHN, and one assigned to received home-visits and drop-in centre access. Because there were four LGAs in the small group, two LGAs were randomly assigned to be comparison LGAs.

The interventions commenced in LGAs in July 2012 and ran for a nine month period until March 2013. Data collection is now complete. Analysis and final writing up is underway. Final results are expected in 2015.

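### LGAs are randomised (4, 3 and 3 per arm), but clustering is adjusted for only at MCH-centre level, so residual between-LGA variation has no error term

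*Protocol article*

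**What the plan says.** On allocation, the protocol (Randomisation procedure) is explicit: "The unit of randomisation will be the LGA". Trial status reports the outcome: "The remaining ten LGAs, comprising three large, three medium and four small LGAs, agreed to participate and be randomised". One LGA per size group went to each arm, with one exception: "Because there were four LGAs in the small group, two LGAs were randomly assigned to be comparison LGAs". That makes 4 comparison LGAs and 3 in each intervention arm.

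On clustering, the Sample size section says "While the unit of randomisation is the LGA, the MCH centres form the clusters". The analysis follows suit (Data analysis, Primary outcome): "In all analyses, adjustment will be made for clustering at the MCH centre level, and the LGA strata" are allowed for. The same paragraph plans a multivariate logistic model to "adjust for known potential confounders, as well as for the baseline breastfeeding rates of each LGA", with results reported as adjusted odds ratios. The Secondary outcomes section applies the same method to every comparison of breastfeeding percentages.

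The article states no LGA random effect, LGA-level robust variance or LGA-level summary analysis.

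**The concern.** Every MCH centre in an LGA gets the arm its LGA drew. Treating centres as the independent clusters credits each arm with dozens of randomised units when it has three or four. Anything that shifts a whole LGA up or down moves the estimated effect, and a centre-level standard error hardly registers it.

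The protocol gives reason to expect such shifts. Each intervention LGA recruits its own SILC-MCHNs, and each LGA with a drop-in centre chooses and promotes its site. The Background cites six-month rates of 68% and 32% in two Victorian LGAs, although these are contrasting examples from across the state and not the trial's LGAs.

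The sample size reasoning itself begins at LGA level, "assuming a standard error for the average breastfeeding rate in each LGA of 5" per cent, and arrives at a number of LGAs per arm. The analysis then leaves that level out of the error term. At stake is whether a significant result for either primary hypothesis could be no more than a difference between a few municipalities.

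**Working it through.** **The plan's own figure.** The aim is to "detect an increase in the overall breastfeeding rates at four months from 48% to 58" per cent. Take the 5% as the SD of an LGA's average rate, with two-sided alpha 0.05 (sides not stated, so assumed) and 80% power:

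LGAs per arm = 2 × 0.05² × (1.960 + 0.842)² / 0.10² = 3.92, rounded up to 4.

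This reproduces the stated figure of about 4 LGAs per arm. The text then ties the 5% to 374 women per arm, as if it were sampling error. On that reading, n per LGA = 0.48 × 0.52 / 0.05² ≈ 100, or about 399 for four LGAs, which is near 374 but not equal to it. A standard two-proportion formula for 48% v 58% gives 390. So the 5% is ambiguous; the between-LGA reading is the one that yields 4 LGAs.

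**Why a small LGA SD matters.** At a rate of 48%, LGA-level ICC = SD² / (0.48 × 0.52). With 1000 births a year and 7 analysed months (9 less the 2-month run-in), m = 1000 × 7/12 ≈ 583 infants per LGA. The variance inflation from the LGA level alone is 1 + 582 × ICC:

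- SD 1 point: ICC 0.0004, inflation 1.23
- SD 2 points: ICC 0.0016, inflation 1.93
- SD 3 points: ICC 0.0036, inflation 3.10
- SD 5 points: ICC 0.0100, inflation 6.83

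For scale, the plan's centre-level ICC of 0.02 implies a between-centre SD of √(0.02 × 0.2496) = 7.1 points. If 10% of that variance lay between LGAs (an assumption), the LGA SD would be 2.2 points; at 25% it would be 3.5 points.

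**Type I error by simulation under no effect.**

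- From the protocol: ten LGAs in strata of 3/3/4, allocated as reported; rate 48%; centre ICC 0.02; 7 months of outcome data; 3 months of baseline.
- Assumed: about 86 births per centre, so about 12 centres in an LGA of 1000 births (the text calls 86 a number of centres, but 1 + 85ρ uses it as a cluster size); LGA sizes either all 1000 births or 3000/1500/700 by stratum; correlation of 0.5–0.95 between an LGA's baseline and outcome-period rates. The LGA SD is that within size stratum before baseline adjustment. Individual confounders were not simulated, so read it as what remains after them.
- Test: linear-probability stand-in for the logistic model, with stratum terms, centre-robust standard errors and a cut-off of 1.96; 2,500–3,000 replicates, two comparisons each.

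| LGA SD (points) | Without LGA baseline rate | With LGA baseline rate |
|---|---|---|
| 1 | 7–8% | 5–6% |
| 2 | 11–17% | 6–12% |
| 3 | 17–27% | 9–22% |
| 5 | 30–45% | 12–38% |

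With an LGA SD of zero and no baseline adjustment, the rate is 5–6%, so the excess comes from the LGA level. If the 5% is the total SD of an LGA mean and includes centre-level sampling, the LGA part is √(0.05² − 0.2496 × 2.7/1000) = 4.3 points. The rate is then 27–40% without baseline, and 15–24% with it at correlation 0.8.

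An analysis of the ten LGA means on arm and stratum, with or without the baseline rate, using t on 5 or 4 degrees of freedom, gave 4.4–5.3% wherever it was run (SD 2, 4.3 and 5 points).

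**Power of a valid analysis, 10-point effect, LGA SD 5 points, plain two-sample t-test.**

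- 3 v 4 LGAs: SE = 5 × √(1/3 + 1/4) = 3.82; 10/3.82 = 2.62; power 56% on 5 df (74% by the normal formula).
- 4 v 4 LGAs: SE = 5 × √(1/4 + 1/4) = 3.54; 10/3.54 = 2.83; power 66% on 6 df (81% by the normal formula).

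**The case against.** The best defence is that the plan does not neglect the LGA. Allocation is stratified by LGA size, the strata are in the model, individual confounders are adjusted for, and each LGA's own baseline rate is a covariate. The baseline includes the same 24-hour feeding item as the primary outcome. Eligibility is also restricted to LGAs below the state average at discharge, which should narrow the spread. A reader might infer that between-LGA variation is ignored outright. The documents do not support that, and type I error figures computed without the baseline rate overstate the problem for the adjusted analysis that will be reported.

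The defence also holds on magnitude. The protocol gives no between-LGA variance, before or after adjustment, and its 5% is called a standard error and linked to a number of women. With an SD of 1 point and baseline adjustment, the planned test is close to nominal.

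What does not stand is the step from partly explained to safe. Covariates remove variation but supply no error term for the rest. The baseline covers only three months and is named only for the multivariate model. The planned method is valid only if residual LGA variance is practically zero, which the protocol never argues. Nor can this be left to an unseen analysis plan, because the protocol itself fixes the clustering level for all analyses.

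**Conclusion.** The structural defect is certain: the clustering adjustment sits one level below randomisation, with only ten randomised units. Intervals and P values for both primary comparisons, and for the breastfeeding-percentage secondaries, are too optimistic whenever LGAs differ beyond size stratum, baseline rate and individual covariates.

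The size is conditional. With the planned baseline adjustment, type I error runs from about nominal (SD 1 point) to 12–38% (SD 5 points). It is tempting to say that the false-positive rate is several times 5%. The documents support only that it can be: the upper figures require the 5% to be a between-LGA SD, which is one reading of an unclear sentence, and they also depend on assumed LGA sizes and baseline correlations. The matter should be settled before either primary result is reported.

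**What to change.** Make inference for both primary comparisons respect the LGA, with the MCH centre kept as a lower level. Either of these would do:

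- Covariate-adjusted LGA-level summaries from an individual-level model without arm, then a regression of the ten values on arm and size stratum using t on 5 degrees of freedom, or on 4 if the LGA baseline rate is included.
- A mixed model with random effects for LGA and for centre within LGA, and small-sample degrees of freedom.

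Correct the Sample size sentence that makes MCH centres the clusters, say what the 5% represents, and use the same method for the three- and six-month outcomes.

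Data collection was complete at publication, so this changes analysis and reporting only. The cost is wider intervals and lower real power: about 56% for the 3 v 4 comparison actually available, and 66% even for 4 v 4, if the LGA SD is 5 points, against the 80% planned. Baseline adjustment may recover some of this at the price of one degree of freedom. The number of LGAs can no longer be changed. The shortfall is a limit of the design that centre-level clustering conceals, and the report should say so.

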#### Secondary outcomes

All comparisons that involve percentages of breastfeeding will be undertaken using the same method as the primary outcome, with each intervention group compared to the standard care group using intention to treat analysis. Comparison of means will be undertaken for continuous variables such as breastfeeding duration using t-tests where data were normally distributed or medians compared otherwise using Mann-Whitney U tests.

Data obtained from women’s surveys will be explored using descriptive statistics. Analysis for pre-coded responses will be undertaken using descriptive statistics, and frequencies and percentages presented. Outcomes will be presented by trial arm; with statistical comparisons undertaken when appropriate using the chi-square test. Women’s responses to open-ended questions will be analysed inductively and grouped into analytical descriptive categories [46]. The categories will be discussed by the research team and final themes agreed. Comparisons will be made between trial arms where possible.

Data from the focus groups with SILC-MCHNs and face-to-face interviews with MCH co-ordinators or managers will be transcribed and grouped into analytical descriptive categories using basic thematic analysis [46]. SILC-MCHN survey data will be analysed using a mix of quantitative (for pre-coded responses) and qualitative (for open-ended responses) methods.

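### The tests named for breastfeeding duration and other survey responses ignore randomisation by LGA, and the duration comparison makes no provision for mothers still breastfeeding at the six-month survey

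*Protocol article*

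**What the plan says.** All references are to the protocol article.

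- **Randomisation procedure:** "The unit of randomisation will be the LGA". **Trial status:** "The remaining ten LGAs, comprising three large, three medium and four small LGAs, agreed to participate and be randomised"; four went to comparison and three to each intervention arm.
- **Data analysis, Primary outcome:** "In all analyses, adjustment will be made for clustering at the MCH centre level".
- **Data analysis, Secondary outcomes:** the primary method is carried over for one class of outcome: "All comparisons that involve percentages of breastfeeding will be undertaken using the same method as the primary outcome". For duration the text reads "Comparison of means will be undertaken for continuous variables such as breastfeeding duration using t-tests where data were normally distributed". Where that condition fails, a rank test on medians (Mann-Whitney) takes its place. For other pre-coded survey responses the main presentation is descriptive, with "statistical comparisons undertaken when appropriate using the chi-square test".
- **Outcome data and Table 1:** duration of any and only breastfeeding comes from the postal survey. Women "will be sent a questionnaire when their infants are six months of age". Age at cessation is listed only in the survey column. Infant age and feeding in the last 24 hours are also collected there. MCH centre postcode is listed only at the four- and eight-month KAS visits.
- **Sample size:** any breastfeeding in the below-average LGAs is put at 81% at discharge, 53% at three months, 48% (estimated) at four and 39% at six. The design effect is 2.70, from an ICC of 0.02 and a cluster size of 86.

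**The concern.** There are two separate difficulties.

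**Clustering.** A t-test, a Mann-Whitney test and an ordinary chi-square test contain no term for the LGA or the MCH centre. If women in one area resemble each other, the standard error is too small and P values for duration, breastfeeding problems, satisfaction and service use are too small as well. The sentence on adjustment in all analyses does not settle this. If it covers only the section in which it stands, the secondary tests are unadjusted. If it covers everything, it contradicts the tests named in the next section. It also refers to MCH centres, whereas LGAs were randomised.

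**Censoring.** A mother still breastfeeding when she completes the survey has no cessation age. The article does not say how she enters a comparison of mean or median duration. If she is left out, the comparison is restricted to mothers who stopped early, and the women in whom the intervention worked best are removed.

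**Working it through.** **1. Reproducing the plan's design effect.** 1 + 85 × 0.02 = 2.70, as stated.

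**2. True size of a test that ignores clustering.** Size = 2 × [1 − Φ(1.96/√DEFF)]. At DEFF = 2.70: 1.96/1.643 = 1.193, so the size is 0.233, about 23% against a nominal 5%.

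**3. The same for the survey.** Survey clusters are smaller. With the run-in excluded, 7 of 9 months contribute data. The response rate is not given, so I assume 30–100%.

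| Level | Women per cluster | ICC | DEFF | True size |
|---|---|---|---|---|
| MCH centre, 30% response | 86 × 7/12 × 0.3 = 15 | 0.02 (plan) | 1.28 | 8% |
| MCH centre, 100% response | 86 × 7/12 = 50 | 0.02 (plan) | 1.98 | 16% |
| LGA, 30% response | 1000 × 7/12 × 0.3 = 175 | 0.002 (assumed) | 1.35 | 9% |
| LGA, 100% response | 1000 × 7/12 = 583 | 0.02 (assumed) | 12.65 | 58% |

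The article gives no LGA-level ICC, so the last two rows show a range and are not an estimate.

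**4. Share censored, any breastfeeding.** 39% of all infants, or 39/81 = 48% of those breastfeeding at discharge. If a 10-point gain lasted to six months, the intervention figures would be 49% and 49/81 = 60%.

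**5. Effect of the handling of mothers still breastfeeding.** Take women breastfeeding at discharge and a piecewise-linear curve through the plan's figures divided by 81%: 1 at birth, 0.654 at three months, 0.593 at four, 0.481 at six.

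The restricted mean to six months is the area under the curve. Control: 3 × (1 + 0.654)/2 + (0.654 + 0.593)/2 + 2 × (0.593 + 0.481)/2 = 4.18 months. The mean among those who stopped is (restricted mean − 6 × S6)/(1 − S6), where S6 is the share still breastfeeding at six months. Control: (4.179 − 2.889)/0.519 = 2.49 months.

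I used two effect models, each reaching 58% of all infants at four months. The proportional model has hazard ratio ln(58/81)/ln(48/81) = 0.638.

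| Effect model | Restricted mean, control vs intervention | Gain | Stoppers only | Gain | Lost |
|---|---|---|---|---|---|
| Proportional hazards | 4.18 vs 4.73 | 0.55 | 2.49 vs 2.59 | 0.10 | about 82% |
| Constant 10 points (at 3, 4 and 6 months) | 4.18 vs 4.73 | 0.56 | 2.49 vs 2.80 | 0.31 | about 44% |

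For full duration a tail must be assumed. With an exponential tail of mean 6 months and the constant-difference model, the true gain is about 1.30 months. Stoppers only show 0.31, a loss of about 76%.

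**6. Medians.** Among all infants the control median is 3 + (53 − 50)/(53 − 48) = 3.6 months and is observed. Among women breastfeeding at discharge it is about 5.7 months in control and is not reached by six months in the intervention arm.

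**The case against.** The other side has good arguments.

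- **Nothing says that mothers still breastfeeding will be dropped.** A reader might infer it, and so infer that the duration result will be biased towards no effect. The documents do not support that: the survey collects current feeding and infant age, so these mothers can be identified and kept. Entering six months for them gives essentially the restricted mean, and a Mann-Whitney test with them tied at one common age is valid apart from clustering. What stands is that the article does not choose among these options, and they give different answers.
- **The t-test is conditional on normality.** With 39–48% of values piled up near six months, the plan's own rule would lead to medians and ranks. This weakens the objection to the t-test, but not the clustering point or the need to define how censored durations are handled.
- **The scope is narrow.** A reader might take every survey outcome to be tested by chi-square. That is not so: breastfeeding percentages use the primary method, other responses are mainly descriptive, and duration is in no stated hypothesis.
- **Adjustment is not impossible.** Design-adjusted versions of chi-square exist. Although the survey column has no MCH centre postcode, it has the mother's postcode, and the promise under Dissemination of separate survey results for each LGA implies that LGA is known. The article names no adjusted version, so the two sections still need reconciling.
- **Only breastfeeding is different.** The 39% figure is for any breastfeeding, and the article describes exclusive breastfeeding to six months as uncommon. The censored share for only breastfeeding cannot be derived from the article.

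**Conclusion.** The point holds for secondary and survey outcomes. Done as written, the tests named for duration and pre-coded responses would ignore cluster randomisation, and the general sentence on clustering either does not reach them or contradicts them. At the plan's design effect the true size is about 23%. For the survey itself the direction is secure but the size is not: 8–16% at centre level and 9–58% at LGA level, resting on an assumed response rate and, at LGA level, an assumed ICC. No scenario examined returns the test to 5%. A single narrow figure for the survey would claim more than the article allows.

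On censoring, a mean of full duration of any breastfeeding is not estimable from a six-month survey with about 39% of infants (48% of those breastfeeding at discharge) still breastfed. Analysing stoppers only would lose between about 44% and 82% of the gain to six months, depending on the effect model, and about 76% of the full-duration gain under the assumed tail. That is the consequence of a choice the plan leaves open, not of one it has made.

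The primary outcome and the three- and six-month breastfeeding percentages are not touched by this point.

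**What to change.** 1. Analyse duration of any and of only breastfeeding as time-to-event, censored at infant age at survey completion, retaining women still breastfeeding. Kaplan-Meier curves with a restricted mean to six months, or Cox or discrete-time regression, would all serve.
2. For between-arm comparisons of duration and other survey responses, replace the t-test, Mann-Whitney and ordinary chi-square with methods that account for clustering at LGA level and the size stratum, with a small-sample correction for ten LGAs. Otherwise report these contrasts descriptively, without P values.
3. Reword the sentence on clustering so that its scope is plain and agrees with the tests named for secondary outcomes.

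The cost is wording and modest programming. Cessation age and infant age at survey are already collected, and LGA membership appears to be available. The price is wider intervals and fewer nominally significant secondary results. Because the article reports data collection complete and analysis under way, the change should be dated and, if possible, made before between-arm survey results are seen.
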